### Sample size calculation and allocation

The sample size was calculated using G*Power 3.1 software for a two independent samples t-test. The primary outcome was pre-hospital delay intention (PHDI). A large effect size (Cohen’s d = 0.80) was adopted, which was justified by a previous study in patients with high-risk diabetic foot that reported a large effect size on pre-hospital delay intention [30]. The type I error rate (α) was set at 0.05 (two-tailed), and the statistical power (1 − β) was set at 0.85 [31]. The calculation yielded a required sample size of 30 participants per group. Accounting for an anticipated 15% attrition rate during follow-up, the final target sample size was set at 35 patients per group (total N = 70).

All the participants will be randomly divided into control group (n = 35) and intervention group (n = 35) upon admission. Randomization will be performed automatically by Microsoft Excel at enrollment. The “RAND ()” function in Microsoft Excel will be used to generate a series of random numbers by an independent researcher and kept in a sealed, opaque envelope. These numbers will be served as the basis for patient allocation into either the control group or intervention group.

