### Outcome measures

Schedule of enrolment, interventions, and assessments are presented in Fig 1. Baseline (T 0) data will be collected right after participants’ eligibility is determined and consent signed. Before and after completing 4 weeks intervention (T1), patients’ pre-hospital delay intentions, foot care knowledge, foot care self-efficacy, foot care behaviors, blood glucose, blood pressure, weight, and DPN syndrome, will be assessed.

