### Statistical analyses

All statistical analyses will be performed using SPSS version 27.0 (IBM Corp., Armonk, NY, USA). Continuous variables with a normal distribution will be expressed as mean and standard deviation, while those with a non-normal distribution will be presented as median and interquartile range. Categorical variables will be summarized as frequencies and percentages and compared using the chi-square test or Fisher’s exact test as appropriate.

Longitudinal changes in primary and secondary outcomes measured at baseline, one month post-intervention, and three months post-intervention will be assessed using repeated-measures analysis of variance. The raw outcome value measured at each time point will serve as the dependent variable. Group will be treated as the between-subjects factor, and time as the within-subjects factor.

For secondary outcomes, the Bonferroni method will be applied to adjust P-values for multiple comparisons to control the type I error rate. Both intention-to-treat and per-protocol analyses will be performed. For the intention-to-treat analysis, missing data will be handled using multiple imputation under the missing at random assumption, with 20 imputed datasets generated and results pooled according to Rubin’s rules. A sensitivity analysis using complete case analysis will be conducted under the missing not at random assumption to assess the stability of the findings. Statistical significance will be defined as a two-sided adjusted P-value of less than 0.05. The study flowchart is presented in Fig 2.

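### Holm's step-down adjustment would control the same familywise error for the secondary outcomes as the planned Bonferroni adjustment and never reject less: a cheap, mostly modest gain

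*Protocol article*

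**What the plan says.** The Statistical analyses section of the protocol article fixes the method in one sentence: for the secondary outcomes, "the Bonferroni method will be applied to adjust P-values for multiple comparisons", with type I error control as the stated purpose. The decision rule follows: "Statistical significance will be defined as a two-sided adjusted P-value of less than 0.05". The section gives neither the family nor the number of tests in it, and it mentions no simultaneous confidence intervals.

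The candidates for the family have to be collected from elsewhere. The Outcome measures section says that, besides pre-hospital delay intention, "foot care knowledge, foot care self-efficacy, foot care behaviors, blood glucose, blood pressure, weight, and DPN syndrome, will be assessed". Going through the outcome descriptions one by one gives ten measures:

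- the knowledge (ADKnowl), self-efficacy (DSES), behaviour (NAFF) and neuropathy (TCSS) scores: 4
- fasting glucose, post-prandial glucose and HbA1c: 3
- systolic and diastolic blood pressure: 2
- weight or BMI: 1

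Ulcer incidence is described as a safety outcome and is not counted. Only the primary outcome is powered; no effect size or power is given for any secondary outcome.

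**The concern.** Bonferroni compares every P-value with 0.05/m. Holm does so only for the smallest P-value and relaxes the threshold after each rejection, with the same guarantee on the familywise error. When a plan reports adjusted P-values and makes no use of matching simultaneous intervals, single-step Bonferroni is the weaker of two equally safe options.

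This has some bearing here because the Aim and hypothesis section expects improvement in knowledge, self-efficacy, behaviour, foot health, blood glucose and blood pressure. Holm gains most when many outcomes respond, and the trial is small. At stake is how often true secondary effects reach adjusted significance. The validity of any claim is not in question.

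**Working it through.** **1. The plan's own figure.** Inputs from the sample size section: "A large effect size (Cohen’s d = 0.80) was adopted", two-sided 0.05, and "the statistical power (1 − β) was set at 0.85". The normal approximation is n = 2(1.960 + 1.036)²/0.80² = 28.1, so 29 per group. The exact noncentral t gives power 0.849 at 29 and 0.861 at 30, so 30 per group. The plan's figure is reproduced ("The calculation yielded a required sample size of 30 participants per group"), and 30 per arm is used below.

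**2. Why Holm cannot do worse.** Order the P-values p(1) ≤ … ≤ p(m). Holm rejects in order for as long as p(k) ≤ 0.05/(m − k + 1). With m = 10 the thresholds are 0.0050, 0.0056, 0.0063, 0.0071, 0.0083, 0.0100, 0.0125, 0.0167, 0.0250 and 0.0500. Bonferroni uses 0.0050 throughout. Every Holm threshold is at least as large, so every Bonferroni rejection is also a Holm rejection. The first thresholds are equal, so the chance of at least one rejection is identical. This holds for any family of two or more tests.

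**3. What familywise control costs.** Exact power at 30 per arm, two-group t-test:

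| m | Level 0.05/m | Power, d = 0.8 |
|---|---|---|
| 1 (unadjusted) | 0.05 | 86.1% |
| 6 | 0.0083 | 64.3% |
| 10 | 0.0050 | 57.4% |
| 12 | 0.0042 | 54.9% |

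For d = 0.5, power falls from 47.8% unadjusted to 17.5% at m = 10.

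**4. What Holm recovers.** Simulation with 40,000 runs per scenario, m = 10 and 30 per arm. Effect sizes and correlations are assumptions, because the article gives none for the secondary outcomes. Average power per true effect at correlation 0.3, with the range of gains over correlations 0, 0.3 and 0.5:

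| True effects | Bonferroni | Holm | Gain at 0.3 (points) | Range of gain |
|---|---|---|---|---|
| 3 at d = 0.5, 7 null | 17.2% | 17.7% | 0.5 | 0.4 to 0.6 |
| 3 at d = 0.8, 7 null | 57.3% | 59.1% | 1.8 | 1.7 to 1.8 |
| all 10 at d = 0.5 | 17.5% | 20.8% | 3.3 | 1.9 to 4.2 |
| all 10 at d = 0.8 | 57.2% | 70.4% | 13.1 | 12.4 to 14.3 |

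In expected true findings at correlation 0.3, that is 1.72 against 1.77 of 3 in the second row, and 5.7 against 7.0 of 10 in the last.

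Holm never rejected less than Bonferroni in any run. The chance of at least one rejection was the same in every scenario, for example 87.3% under both with three effects of 0.8 at correlation 0.3.

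**5. Share recovered.** At d = 0.8 and m = 10 the adjustment costs 86.1 − 57.4 = 28.7 points. Holm returns about 1.8 of these with three responders, and 12.4 to 14.3 if all ten respond. Even in the most favourable case, half or more of the loss remains.

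**6. Error rate.** With all ten null at correlation 0.3, the simulated familywise error was 4.6% under both methods. With three effects of 0.8 it was 3.3% for Bonferroni and 4.1% for Holm. At correlation 0 with all null, both gave 5.0%, against the exact value for ten independent tests of 1 − 0.995¹⁰ = 4.9%, which is within simulation error.

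**7. Other family sizes** (correlation 0.3, d = 0.8). With three responders the gain is 64.5% to 67.9% for m = 6 and 55.0% to 56.3% for m = 12. If all respond it is 64.5% to 76.5% and 54.9% to 68.1%.

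**The case against.** The strongest case against raising this is that nothing in the section is wrong. Bonferroni is valid, prespecified and widely understood, and it contradicts nothing else in the article. That stands: this is a point about efficiency only.

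Three further objections limit its size.

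- **The family is inferred.** The sentence refers only to multiple comparisons and comes soon after a repeated-measures analysis with three time points, so it could mean outcomes, time-point contrasts or both. A reader might infer that the plan divides 0.05 by ten; the article does not say so. Leaving the family to a fuller analysis plan is common and is not held against the article here. Holm's advantage holds for any family, but its size depends on m.
- **The large gains rest on an unsupported assumption.** A reader might conclude that Bonferroni costs this trial a large share of its secondary findings. That needs all ten measures, including HbA1c, both blood pressures and weight, to shift by 0.8 standard deviations. The article gives d = 0.80 for the primary outcome only. With three responders the gain is about 0.5 to 2 points.
- **Bonferroni does buy something.** It has simple matching simultaneous confidence intervals, and Holm does not. It would therefore be too strong to say that the power is given up for nothing. The advantage counts for little here, because the article judges significance by adjusted P-values and announces no such intervals.

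The simulation also uses two-group t-tests in place of the planned repeated-measures analysis. This affects the sizes shown, not the ordering of the two methods.

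**Conclusion.** The point holds as a cheap improvement. For any family of two or more secondary tests, Holm gives the same familywise guarantee as the planned Bonferroni adjustment and never rejects less.

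On the assumption of a ten-measure family, 30 evaluable per arm and the effect sizes shown, the gain in power per true effect is about 0.5 to 2 points with three responders and about 2 to 4 points if all ten have d = 0.5. It reaches about 12 to 14 points only if all ten have d = 0.8. The chance of at least one significant secondary outcome does not change. The documents do not support reading this as an error in the plan or as a threat to its conclusions.

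**What to change.** In the Statistical analyses section, replace Bonferroni with Holm for the adjusted P-values of the between-group tests across the secondary outcomes, and name the outcomes in that family. The Holm-adjusted P-value for the k-th smallest is the maximum over j ≤ k of min{1, (m − j + 1)p(j)}. Report unadjusted 95% confidence intervals beside the P-values and label them as unadjusted.

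The cost is about a sentence of text and a calculation on the ordered P-values; no further data or patients are needed. The timeline section describes the study as not yet recruiting, so the change can be prespecified before any data exist. The small downside is that an unadjusted interval may exclude zero where the Holm-adjusted P-value is above 0.05, which the label should make clear. Which time point or contrast the between-group test uses, and the status of the 3-month assessment, are separate matters and need not change for this fix.

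### The complete-case sensitivity analysis is labelled missing not at random, but it assumes more than the main imputation and cannot test informative dropout

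*Protocol article*

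**What the plan says.** All of the missing-data plan is in the Statistical analyses section of the protocol article.

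- Main intention-to-treat analysis: "missing data will be handled using multiple imputation under the missing at random assumption, with 20 imputed datasets generated", pooled by Rubin's rules.
- Sensitivity analysis: "A sensitivity analysis using complete case analysis will be conducted under the missing not at random assumption to assess the stability of the findings".
- Model: outcomes at baseline, one month and "three months post-intervention will be assessed using repeated-measures analysis of variance". On the variables: "The raw outcome value measured at each time point will serve as the dependent variable". On the factors: "Group will be treated as the between-subjects factor, and time as the within-subjects factor". No covariate is named.

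The Sample size calculation and allocation section expects real losses: "Accounting for an anticipated 15% attrition rate during follow-up, the final target sample size was set at 35 patients per group (total N = 70"). Under Data collection and management, patients who stop the intervention are asked to allow some outcome data to be taken from their medical records. The primary outcome is a seven-item questionnaire scored 7 to 28, with higher scores worse.

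**The concern.** The sentence pairs a named method with an assumption that the method does not make. An MNAR analysis must say how unobserved outcomes differ from observed ones after allowing for what was recorded. Complete case says nothing about this; it drops the patients. It can tolerate missingness that depends only on covariates in the model, but the factors here are group and time alone.

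This is the only missing-data sensitivity analysis stated, and its declared purpose is to show that the findings are stable. If it agreed with the imputation, the trial report could claim robustness to informative dropout that was never examined. The question is a fair one here: patients are not blinded, the primary outcome is an attitude that may be related to staying in the study, and medical records are unlikely to hold a PHDI score for those who leave.

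**Working it through.** **Inputs from the article.** d = 0.80, two-sided alpha 0.05, power 0.85, 30 evaluable per group, 15% attrition, 35 recruited per group. The dropout mechanisms, the correlations between visits and the dropout-completer differences below are assumptions. Effects are in SD units, and a positive effect means lower delay intention in the intervention arm.

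**1. The plan's own figure.** The noncentral t calculation gives power 0.849 at 29 per group and 0.861 at 30, so 30 is reproduced. With 15% loss, 35 × 0.85 = 29.75, or about 30 completers per arm.

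**2. What each method assumes.**

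| Analysis | Dropout may depend on | Label in the article |
|---|---|---|
| Multiple imputation | observed data, such as earlier scores | MAR |
| Complete case, group and time only | arm, but not outcomes within arm | MNAR |
| A genuine MNAR method | the unobserved outcome itself | none planned |

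The sensitivity analysis thus moves from MAR towards missing completely at random (MCAR), away from MNAR.

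**3. Large-sample simulation.** 400,000 patients, three visits, about 15% missing at the last visit, true effect 0. Dropout in the intervention arm depends on the previous score (MAR) or on the final score itself (MNAR), with log-odds 1 per SD; control dropout is random. Entries are bias in favour of the intervention, at correlations 0.3 / 0.5 / 0.7.

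| Mechanism | Complete case | MAR imputation |
|---|---|---|
| MAR | 0.05 / 0.08 / 0.11 | 0 / 0 / 0 |
| MNAR | 0.15 / 0.15 / 0.15 | 0.13 / 0.10 / 0.07 |

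Under MCAR both are unbiased. Under MAR, complete case is biased where imputation is not. Under this MNAR mechanism both err the same way and complete case errs more, so it neither corrects nor brackets the bias.

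**4. Size of the complete-case bias.** If a fraction f of an arm is missing and its dropouts are D worse than completers, the completers' mean is too favourable by f × D. For the difference between arms:

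bias = f(intervention) × D(intervention) − f(control) × D(control)

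Intervention arm only, f = 0.15:
- D = 0.5: 0.075 SD, or 0.075/0.80 = 9% of the planned effect
- D = 1.0: 0.150 SD, or 19%
- D = 1.5: 0.225 SD, or 28%

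Equal f and D in both arms: 0.15 × 1.0 − 0.15 × 1.0 = 0.

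**5. The same selection rule in one arm or both.** Dropout logit = −2.2 + 1.5 × PHDI in SD units, true effect 0.80.

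| Where the rule applies | Dropout, intervention / control | Complete-case effect |
|---|---|---|
| Intervention only, standardised within arm; control random | 17% / 15% | 0.99 |
| Both arms, standardised within arm | 17% / 17% | 0.80 |
| Both arms, on the common PHDI scale | 7% / 17% | 0.70 |

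The direction of the bias is therefore not fixed by saying that patients with high delay intention leave more often. It depends on the arms.

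**6. Effect on significance.** With 30 per arm, SE = √(2/30) = 0.258 and the critical t is 2.00. An effect of 0.80 shifted by the largest value above leaves 0.80 − 0.225 = 0.575, and t = 0.575/0.258 = 2.2: still significant. Significance needs at least 2.00 × 0.258 = 0.52, so an observed effect between 0.52 and 0.52 + 0.225 = 0.74 would lose it somewhere within the 0 to 1.5 SD range. This is a two-sample approximation that ignores the extra variance from imputation.

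**The case against.** Four points can fairly be made for the plan.

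- The primary analysis is untouched. Multiple imputation under MAR with 20 datasets is a sound main method, and the error sits in one sentence on a sensitivity analysis. This stands, and it limits the weight of the point.
- Complete case is a customary companion to imputation, and comparing the two is informative about MCAR versus MAR. This stands too: the analysis can be kept, and only its label and the inference drawn from it are wrong.
- A reader might infer that informative dropout would inflate the result. The article gives neither dropout by arm nor reasons for it. Overstatement follows only if dropout is informative mainly in the intervention arm; the same rule in both arms gives no bias or an understatement.
- A reader might also infer that this is the chief threat to the primary result. That is not shown: at the planned effect, even a 1.5 SD shift in 15% of one arm leaves the result significant. Retention measures are planned as well, although record-based follow-up is unlikely to recover the questionnaire.

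None of this rescues the sentence as written. The protocol chose to examine MNAR, and the method it names cannot do so.

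**Conclusion.** The point holds. The statement is wrong as written, and it is not a detail left to an analysis plan, because the article names both the method and the assumption and the two do not match. As planned, no stated analysis tests departure from MAR, and agreement between complete case and imputation would not show robustness to informative dropout.

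The size is conditional. With 15% missing and dropouts 0.5 to 1.5 SD worse in the intervention arm alone, complete case overstates the effect by 0.08 to 0.23 SD (9% to 28% of 0.80). With the same mechanism in both arms the bias can be zero or reversed (about 0.70 against 0.80). These mechanisms are assumed. The documents do not support a prediction that the trial's effect will be overstated, nor that its primary conclusion would be overturned.

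**What to change.** 1. Relabel complete case as a supplementary analysis that assumes dropout is unrelated to outcome within arm.
2. Add a genuine MNAR analysis of PHDI. One option is delta-adjusted multiple imputation on the 20 datasets already planned: add shifts to the imputed scores, for example 0 to 1.5 SD, varied separately in each arm and including the intervention arm alone; pool by Rubin's rules; and report the shifts at which significance is lost. Reference-based imputation or another pattern-mixture model would also serve.
3. Settle the choice before unblinded outcome data are seen. The article schedules data collection to end in December 2026.

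The cost is a paragraph of wording and a little more analysis work. No new data are needed, and the primary estimate and sample size stay as they are.

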**Fig 2 pone.0350892.g002:**
[figure not shown]
Flow chart of the RCT study protocol.

### Ethic consideration

This study will be conducted in accordance with the principles of the Declaration of Helsinki. The protocol has been approved by the Ethics Committee of the School of Nursing at Yangzhou University (Approval No. YZUHL20230118).

The intervention is classified as minimal risk, as it involves no invasive procedures and its content aligns with established clinical guidelines. Three specific potential risks have been identified. First, participants may experience anxiety due to heightened awareness of foot ulcer risk; psychological support and counseling will be available. Second, there is a possibility of misunderstanding medical advice; this will be mitigated by using pre-tested educational materials and conducting post-session confirmation of understanding. Third, behavioral overcorrection may occur; moderation education and follow-up monitoring will be implemented to promote safe self-care practices.

All identifiable participant information will be replaced with a unique study code to ensure anonymization. Electronic data will be stored on a password-protected computer with access restricted to authorized personnel, and regular backups will be performed to prevent data loss. Consent forms and case report forms will be kept in locked filing cabinets within a secure research office. Access to identifiable information will be limited to the principal investigator and designated research nurses involved in participant follow-up and clinical care coordination; no other team members will have access to such data.

Participants will receive a compensation of 30 RMB per person to cover time and travel expenses. This amount is consistent with the study budget and local standards for minimal-risk research. In the event of accidental injury resulting from research procedures, necessary medical care and related expenses will be provided, along with appropriate economic compensation in accordance with relevant laws and regulations in China.

If a participant develops an active foot ulcer during the trial period, a standardized management procedure will be followed. The participant will be referred to a diabetic foot specialist within 24 hours. Intervention sessions will be temporarily paused, although the participant will remain included in the intention-to-treat analysis. Weekly follow-up will be conducted, and the event will be reported as a serious adverse event to the ethics committee within 72 hours.

Written informed consent will be obtained from all participants after a detailed explanation of the study’s purpose and significance. Participants will be explicitly informed that participation is voluntary and that they have the unconditional right to withdraw at any time. The control group will receive the equivalent intervention upon study completion.

### Reports the status and timeline of the study

The study is currently in the pre-recruitment phase. Participant recruitment is scheduled to commence on February 1, 2026, and is expected to be completed by May 31, 2026. Data collection is planned to conclude by December 2026. Final results are anticipated to be available by March 2027, following data cleaning, statistical analysis, and interpretation.

## Discussion

DFU continues to pose a significant global health challenge, profoundly affecting patients’ quality of life, the utilization of medical resources, and economic burdens. The decision to seek treatment for DFU involves a complex medical process, which includes accurately identifying DFU symptoms, determining the need for specialized medical care, and ultimately taking appropriate action to seek emergency medical treatment. Failure at any of these stages can lead to pre-hospital delays and worsened outcomes, including increased risks of amputation and mortality, and missed opportunities for life-saving treatments. These delays are often attributed to patients’ lack of awareness and understanding of the severity of DFU, resulting in significant knowledge gaps that frequently lead to delayed medical consultation. For example, a systematic review by Novita et al. highlighted that patients with DFU often lack the necessary self-care strategies and motivation to manage their wounds effectively, leading to prolonged healing times and increased risk of complications. These findings highlighted the urgent need for comprehensive education and support to improve patients’ understanding and management of DFU, thereby reducing pre-hospital delays and improving patient outcomes [46].

Health education is important in mitigating pre-hospital delays among patients with DF, as it enhances illness perception and foot care practices [47,48]. However, traditional interventions often rely on a single theory, which may not address the complex behavioral processes required for effective foot care and timely medical consultation. In contrast, the MTM-based intervention in this study offers a more comprehensive framework by integrating multiple health behavior theories, thereby overcoming the limitations of single-theory interventions. This comprehensive approach ensures sustained behavior change through digital platforms and social networks, which is crucial for preventing DFU and reducing pre-hospital delays. As the fourth-generation models, MTM has individual, social, and environmental applications in developing plans for educational interventions, which is an appropriate framework for developing an education program. To our knowledge, it has not been previously implemented in the population of diabetic patients at risk of foot ulceration.

This study represents the first randomized, parallel-controlled, multicenter trial of foot health education based on the MTM for diabetic patients at risk of foot ulceration within the context of Chinese culture, offering comprehensive and detailed data. This innovative approach uniquely integrates multiple health behavior theories, addressing the complex interplay of emotional, physical, and social factors, which is crucial for initiating and sustaining health behavior change. The MTM-based foot care program comprehensively considers the complex interplay of emotional, physical, and social factors, and is expected to reduce pre-hospital delays and prevent DFU by enhancing patients’ foot care knowledge, foot care self-efficacy, and foot care behaviors. However, this study has several limitations. First, the sample may not be fully representative of all diabetic patients in China due to regional and socioeconomic variations. Second, the intervention’s reliance on self-reported outcomes might introduce recall bias. Lastly, the relatively short follow-up period may limit the assessment of long-term behavioral changes and DFU incidence.

